### Recruitment {15}

Trial participants with stroke are being recruited by clinicians from outpatient clinics at Shunyi Hospital, Beijing Traditional Chinese Medicine Hospital. Moreover, information flyers containing the details of the trial are being posted at outpatient clinics of respective institutions for greater exposure. The researchers will enrol patients in accordance with the inclusion and exclusion criteria on the day of admission. Patient recruitment started in January 2021.

## Assignment of interventions: allocation

### Sequence generation {16a}

Commonly used factors for patient stratification include age, sex, body mass index (BMI), smoking habits, and alcohol consumption habits. In this study, the patients are expected to have a large age gap. Therefore, we have chosen age as the blocking factor. All participants will be randomly assigned to one of two groups (‘hand and foot acupuncture with twelve needles’ group and routine acupuncture group) in a 1:1 ratio. The generation and allocation of a random sequence for group assignment will be conducted by the World Federation of Chinese Medicine Societies in China. A block randomisation method (with a block size of four) will be used to generate the random allocation sequence; opaque sealed envelopes containing the predetermined computer-generated numbers will be used to ensure allocation concealment.

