### Trial design {8}

This is an open-label, single-centre, parallel design, 2-arm (allocation ratio 1:1), superiority, randomised controlled trial. A flow diagram of this study protocol is shown in Fig. 1, and the treatment and outcome measures are presented in Fig. 2.

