### Concealment mechanism {16b}

Random numbers will be placed in sequentially numbered, opaque, sealed envelopes.

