### Implementation {16c}

A doctor who is not involved in this study will store the envelopes with random numbers. The researcher who registers the participants will open the envelopes and assign the participants to the intervention groups.

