## Assignment of interventions: blinding

### Who will be blinded {17a}

In this study, the outcome assessors and data analysts will be blinded, but the participants and researchers will not be blinded.

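### A single published block size of four, in an open-label single-centre trial whose unblinded researchers enrol patients, lets site staff work out about a third of allocations in advance

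*Protocol article*

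**What the plan says.** - **Sequence generation {16a}:** "A block randomisation method (with a block size of four) will be used to generate the random allocation sequence". Only one size is given. Age is the stratifying variable ("Therefore, we have chosen age as the blocking factor"), but no cut-points are given for randomisation.
- **Trial design {8}:** "This is an open-label, single-centre, parallel design, 2-arm (allocation ratio 1:1), superiority, randomised controlled trial".
- **Recruitment {15}:** "The researchers will enrol patients in accordance with the inclusion and exclusion criteria on the day of admission".
- **Who will be blinded {17a}:** assessors and analysts are blinded, but "the participants and researchers will not be blinded".
- **Implementation {16c}:** a doctor outside the study keeps the envelopes, and "The researcher who registers the participants will open the envelopes and assign the participants to the intervention groups".
- **Concealment mechanism {16b}:** "Random numbers will be placed in sequentially numbered, opaque, sealed envelopes".

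**The concern.** With 1:1 blocks of four, the next allocation is fixed as soon as one arm has used its two places. The fourth allocation in a block is therefore always determined, and sometimes the third is too. To exploit this, a person needs the block size, which is printed in the protocol article while recruitment is described as ongoing. They also need the past allocations, which are visible at a single open-label site: the two arms use different point sets, one bilateral and one on the hemiplegic side.

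Envelope concealment stops the next assignment from being read early. It does not stop it from being deduced. Blinded assessment acts after enrolment, so it cannot prevent selection at entry.

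At stake is the comparability of the arms. Some entry decisions need judgement, such as the exclusions for a recurrent stroke or another severe disease that could affect results. If such decisions were influenced by the expected arm, prognosis would differ between arms. The between-group test in the statistical methods section is an unadjusted t or rank-sum test, so the difference would pass into the Fugl-Meyer (FMA) comparison.

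**Working it through.** The protocol gives no predictability figure, so there is none to reproduce.

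**Inputs from the protocol:** block size 4, ratio 1:1, 208 participants (104 per arm).

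**1. Allocations certain in advance.** There are C(4,2) = 6 equally likely blocks. The number of positions already determined in each is:

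| Block | Certain positions |
|---|---|
| AABB | 2 |
| BBAA | 2 |
| ABAB | 1 |
| ABBA | 1 |
| BAAB | 1 |
| BABA | 1 |

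The total is 8 of 6 × 4 = 24 positions, or 33.3%. For 208 participants that is 208/3 = 69.3 expected (simulated 95% range 63 to 76).

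**2. Best guess.** Guess the arm with more places left. The chance of being right at positions 1 to 4 is 1/2, 2/3, 2/3 and 1. The mean is (0.5 + 0.667 + 0.667 + 1)/4 = 17/24 = 70.8%, against 50% if unpredictable.

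**3. Age strata.** The number of strata is not stated. With 2 to 6 equal strata assumed and one tally kept per stratum, simulation gives 32.9% down to 32.1% certain (68.5 to 66.8 participants). The small loss comes from unfinished last blocks.

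**4. Consequence under an assumed selection effect.** The documents give no size for this, so it is an assumption. Suppose enrolled patients' expected FMA change is shifted by +d SD when one arm is guessed and by −d SD when the other is, at every informative guess. With correct-guess rate p:

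- Between-arm bias = 2(2p − 1)d. At p = 17/24 this is 0.833d.
- Standard error of the difference in SD units = √(2/104) = 0.1387.
- One-sided error = 1 − Φ(1.96 − bias/0.1387).

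| Scheme | Multiplier of d | d = 0.10 | d = 0.25 |
|---|---|---|---|
| Fixed blocks of 4, every informative guess used | 0.833 | 8.7% | 32.4% |
| Fixed blocks of 4, only the certain third used | 2 × 1/3 = 0.667 | 7.0% | 22.4% |
| Varying blocks 4/6/8, every informative guess used (p = 0.68) | 0.72 | 7.5% | 25.4% |

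**5. Alternatives.** The varying-block rows are simulated for a recruiter who knows the possible sizes and uses the full allocation history, but is not told where blocks begin and end.

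| Scheme | Certain | Best guess correct |
|---|---|---|
| Fixed 4 | 33% | 70.8% |
| Fixed 6 | 25% | 68.3% |
| Fixed 8 | 20% | 66.6% |
| Varying 4/6 | about 5% | about 69% |
| Varying 4/6/8 | about 2% | about 68% |

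Repeating the 4/6/8 simulation with 2, 3 and 6 equal age strata leaves the certain share at about 2% and the guess rate at about 68%.

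**The case against.** **The design is permissible.** Computer-generated blocks, outside generation and custody, and numbered opaque envelopes are accepted practice, and nothing here contradicts another part of the protocol. That stands: this is a design weakness that can be improved cheaply, not an error in the text.

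**The text does not make one person both gatekeeper and envelope opener.** A reader might infer that whoever opens the envelopes also decides eligibility and sees every allocation. The protocol does not say so. The consent section has a neurologist researcher score the scales used for eligibility, the Implementation section has the registering researcher open envelopes, and the Recruitment section speaks of researchers in the plural. Enrolment on the day of admission also limits discretion over timing. Predictability therefore depends on someone tracking or sharing past allocations and, if randomisation is stratified, on knowing the age cut-points. At one open-label site that is feasible, but it is not shown to happen.

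**The error inflation rests on an assumed input.** A reader might take 9% to 32% as the trial's actual type I error. It is not. The shift has no source in the documents, it is applied in both directions (so favoured and disfavoured patients differ by 0.2 to 0.5 SD), and it requires steering at every informative guess.

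**Varying blocks remove little of that modelled inflation.** This is correct: the range falls only to about 7.5% to 25%. What the change removes is nearly all the certainty. Releasing envelopes later does not hide an arm that has already been inferred.

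**Conclusion.** The concern holds as potential for selection bias. With one published block size of four, an expected 33% of allocations (about 69 of 208; 32% to 33% with 2 to 6 assumed age strata) can be known in advance by anyone at the site who follows the sequence, and 70.8% can be guessed. These figures need only 1:1 permuted blocks of four and a person who tracks past allocations and where blocks start. That every block has size four is read from the single size stated.

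The documents do not show that selection occurred or will occur. The type I error range is an illustration under a stated assumption and should not be quoted as a property of the trial. The change is worth making because it is cheap and acts on the step that randomisation is meant to protect.

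**What to change.** For all unused envelopes, have the body that already generates the sequence issue a new list within age strata with randomly varying block sizes, for example 4, 6 and 8. Withhold the sizes from site staff and from publications until recruitment ends. Certain allocations fall from 33% to about 2%. Best-guess accuracy falls only from 70.8% to about 68%, so the change should not be presented as removing predictability altogether.

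As a supplementary safeguard, the outside doctor who holds the envelopes should release each one only after eligibility and baseline scores are irrevocably recorded. This prevents a decision from being reversed once the arm is seen. It does not reduce predictability.

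The cost is one new list and envelope set and a short amendment. An unfinished last block could leave the arms apart by up to 4 within an age stratum (half the largest block) instead of up to 2. Allocations already made cannot be changed.

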### Concealment mechanism {16b}

Random numbers will be placed in sequentially numbered, opaque, sealed envelopes.

### Implementation {16c}

A doctor who is not involved in this study will store the envelopes with random numbers. The researcher who registers the participants will open the envelopes and assign the participants to the intervention groups.

## Assignment of interventions: blinding

### Who will be blinded {17a}

In this study, the outcome assessors and data analysts will be blinded, but the participants and researchers will not be blinded.

### Procedure for unblinding if needed {17b}

The design is open-label with only the outcome assessors and data analysts being blinded so unblinding will not occur.

## Data collection and management

### Plans for assessment and collection of outcomes {18a}

All researchers, including the acupuncturists, outcome assessors, data collectors, data managers, data entry personnel and statisticians, will undergo training before performing standard procedures and data management. A detailed instruction manual will be prepared to ensure consistency and standardisation of data collection and assessment. All data of the participants will be recorded in case report forms (CRFs) by a data collector during the recruitment period and upon the completion of the treatment and follow-up phases. Physicians trained to administer the assessment tools required for this study will be responsible for collecting these data to ensure data are accurate and thoroughness. The physicians will complete the general information form during the assessment. The outcomes will be assessed by a professional from the World Federation of Chinese Medicine Societies.

### Plans to promote participant retention and complete follow-up {18b}

We will follow up the patients for 2 months, either by readmission or outpatient medical consultation. We also plan to hold events to spread awareness about the treatments, which will help ensure patient compliance.

### Data management {19}

All collected data will be entered into the electronic data capture system (EDC, Goodwill Information Technology Co, Ltd., Beijing, China) by trained researchers. To ensure the accuracy of the data, we will randomly check the entered data against the recorded information.

### Confidentiality {27}

The personal data of potential study volunteers as well as the participants will be kept strictly confidential. The participants will be identified by their initials rather than their names. All files will be stored in locked file cabinets which only the researchers will have access to. When the research outcomes are compiled in a publication, no personal information will be disclosed.

### Plans for collection, laboratory evaluation and storage of biological specimens for genetic or molecular analysis in this trial/future use {33}

This trial does not require the collection of biological specimens for storage.

## Statistical methods

### Statistical methods for primary and secondary outcomes {20a}

All analyses will be carried out using IBM SPSS Statistics for Windows, version 22.0 (IBM Corp., Armonk, NY, USA). The measurement data will be expressed as the mean ± standard deviation values. For the outcome measures, the changes in each score and differences between the two groups will be evaluated. Normally distributed data will be analysed using a *t* test, and the non-normally distributed data will be analysed by a rank-sum test. An independent *t* test or rank-sum test will be performed to assess the differences between the two groups. In addition, the count data will be expressed by frequency and analysed by a chi-square test.

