### Who will take informed consent? {26a}

Consent will be obtained by one of the researchers in the presence of a witness. After providing written informed consent, eligible patients will be asked to complete a general information form including their name, sex, age and medical history and complete the same day scale as the baseline assessment. A researcher who is a neurologist with more than 5 years of experience will evaluate the NIHSS, Simplified Fugl-Meyer assessment scale (FMA), modified Ashworth scale (MAS) and Barthel Index (BI) scores for each participant. These scores will be used to determine the eligibility of a patient for the study in accordance with the inclusion and exclusion criteria. The personal information of potential as well as enrolled participants will be collected and stored confidentially.

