### Sample size {14}

The primary efficacy parameter is the change in the FMA score from baseline to 3 months after the treatment [31]. According to our preliminary test and a previous study, the primary efficacy parameter (FMA score) of the control group (rehabilitation treatment) will increase by 12.11 points and that of the treatment group (scalp acupuncture combination rehabilitation treatment) will increase by 25.82 points. The FMA average standard deviation is expected to be approximately 4. Considering a one-sided 5% significance level, 80% power and the above data (*μ*_1_ = 25.82, *μ*_2_ = 12.11, *σ* = 4, *α* = 0.025, 1–*β* = 0.8), according to NCSS-PASS V20.0.3 software (https://www.ncss.com/software/pass/), approximately 86 participants will be required in each group to achieve a sufficient sample size. Accounting for a dropout rate of 20%, each group must include 104 initial participants. Therefore, we plan to include a total of 208 participants divided equally into two groups.

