### Interim analyses {21b}

Descriptive statistics will be used to describe the general status characteristics of patients in detail at baseline, such as gender, age, disease course, and stroke risk factors. Mann-Whitney U test will be used to analyse value changes of FMA, NIHSS, MAS, and BI scores among the groups. Repeated measures analysis of variance (ANOVA) will be used to analyse value changes of FMA, NIHSS, MAS, and BI scores across five testing time points (weeks 0, 2, 4, 8, and 12). Adverse events will be summarised with descriptive statistics.

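### The primary FMA comparison is an unadjusted test on change scores, picked by a normality check, without baseline FMA as a covariate or the age factor used in randomisation: valid, but less precise than it could be

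*Protocol article*

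**What the plan says.** Sample size {14} defines the endpoint: "The primary efficacy parameter is the change in the FMA score from baseline to 3 months after the treatment". Statistical methods for primary and secondary outcomes {20a} adds that "the changes in each score and differences between the two groups will be evaluated". It assigns normally distributed data to a t test and other data to a rank-sum test, and fixes the between-group comparison as an independent t test or "rank-sum test will be performed to assess the differences between the two groups". No covariate or stratum is named.

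Interim analyses {21b} states, with no normality condition, that "Mann-Whitney U test will be used to analyse value changes of FMA, NIHSS, MAS, and BI scores among the groups". It continues: "Repeated measures analysis of variance (ANOVA) will be used to analyse value changes" over weeks 0, 2, 4, 8 and 12. Here too neither baseline FMA as a covariate nor age is mentioned.

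Sequence generation {16a} expects a wide spread of ages and says "we have chosen age as the blocking factor". It gives the method as follows: "A block randomisation method (with a block size of four) will be used to generate the random allocation sequence". Age cut-offs are not given. Baseline FMA is available for everyone, since the consent section {26a} has a neurologist record "Simplified Fugl-Meyer assessment scale (FMA), modified Ashworth scale (MAS) and Barthel Index (BI) scores for each participant".

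**The concern.** The design treats age as important enough to balance by blocking, and baseline FMA is measured in every participant. The named tests can use neither as a covariate. Eligibility is wide (NIHSS 5 to 22, age 35 to 80, 2 weeks to 3 months from onset), so participants will differ greatly at entry. A plain change score leaves regression-to-the-mean noise and chance baseline imbalance in the estimate. If age is prognostic, an analysis that omits it also fails to credit the balance that the blocking has produced.

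Second, the primary test is not settled. The t test concerns a mean difference on the FMA scale and the rank-sum test a shift in ranks. Section {20a} lets the observed distribution decide between them, while section {21b} names the rank test outright. At stake are precision and a single, interpretable primary result, not the validity of the randomised comparison.

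**Working it through.** **1. The plan's own sample size.** Inputs from Sample size {14}: mean changes 25.82 and 12.11, SD 4, α = 0.025, power 80%.

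- Difference: 25.82 − 12.11 = 13.71.
- n per group = 2 × (1.96 + 0.8416)² × (4/13.71)² = 2 × 7.849 × 0.0851 = 1.3, rounded up to 2 (3 with the noncentral t at one-sided 0.025).
- The stated 86 is not reproduced. With 86 per group these inputs give power of practically 100%.
- 86 per group at 80% power corresponds to a difference of about 1.71 with SD 4, or to an SD of about 32 with a difference of 13.71.

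The protocol's figures therefore cannot say what a gain in precision is worth in this trial.

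**2. Change score against ANCOVA.** Let s be the common SD of FMA at baseline and 3 months, and r their correlation. Neither r nor equality of the variances is given, so both are assumptions.

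- Per-participant variance of the change: 2s²(1 − r).
- Residual variance after adjusting for baseline: s²(1 − r²).
- Ratio: (1 − r²) / [2(1 − r)] = (1 + r)/2.
- Power, if the unadjusted test truly has 80% at two-sided 5%: Φ(2.8016/√ratio − 1.96).

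| assumed r | variance ratio | standard error ratio | power |
|---|---|---|---|
| 0.5 | 0.75 | 0.866 | 90% |
| 0.7 | 0.85 | 0.922 | 86% |
| 0.8 | 0.90 | 0.949 | 84% |
| 0.9 | 0.95 | 0.975 | 82% |

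The direction does not need equal variances. If the baseline SD is k times the 3-month SD, the change-score variance minus the ANCOVA variance is proportional to (1 + k² − 2rk) − (1 − r²) = (k − r)², which is never negative.

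A simulation (172 analysed, blocks of four within three assumed age strata of 10%, 45% and 45%, 4,000 runs per setting) agrees. With no age effect, power is 79.6% unadjusted and 90.1% adjusted at r = 0.5, and 79.7% and 85.5% at r = 0.7.

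**3. Leaving out the age factor.** Let R² be the share of variance in FMA change explained by the age strata (not given). With blocking within strata, the unadjusted standard error is too large by the factor 1/√(1 − R²). A nominal two-sided 5% test then has true level 2 × [1 − Φ(1.96/√(1 − R²))].

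| assumed R² | standard error too large by | true level |
|---|---|---|
| 0.01 | 0.5% | 4.9% |
| 0.05 | 2.6% | 4.4% |
| 0.10 | 5.4% | 3.9% |
| 0.20 | 11.8% | 2.8% |

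Simulated at r = 0.7 with an age effect of 0.4 SD per stratum, the mean unadjusted standard error was 0.124 against a true SD of the estimate of 0.118, with type I error 3.9%. That setting has R² = 0.0684/(0.6 + 0.0684) = 0.10, so it matches the third row. The rank-sum test is conservative in the same way.

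**4. Which test.** For changes in FMA, section {20a} gives a t test if the data are normal and a rank-sum test otherwise. Section {21b} gives a Mann-Whitney U test in all cases. For normally distributed data the two sections disagree.

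**The case against.** The strongest reply is that nothing here is an error. Baseline enters by subtraction, a change-score comparison in a randomised trial is unbiased, and its standard error is not distorted by leaving baseline FMA out as a covariate. That stands: the point is efficiency. A reader might infer that the trial ignores baseline FMA altogether; the endpoint definition in Sample size {14} rules that out.

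A reader might also infer that omitting age makes the inference unsafe. It does not. Any effect on the standard error needs age to predict FMA change, for which the protocol gives no evidence, and it then runs in the conservative direction.

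On the protocol's own inputs power is already near 100%, so adjustment would gain almost nothing. This is fair as far as it goes. However, those inputs do not yield 86 per group, and they describe scalp acupuncture plus rehabilitation against rehabilitation, whereas this trial compares two acupuncture regimens. Real power is unknown. For the same reason, the ratios should not be turned into participants saved out of 86: that number has no derivation to scale from.

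The choice between t and rank-sum follows a rule stated in advance, and the data analysts are blinded. The documents therefore do not suggest that the treatment result would drive the choice. What remains is that the quantity estimated depends on the shape of the data, and that the two sections disagree.

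Finally, an article may leave detail to a SAP. But this one names the tests, so the choice itself can be reviewed. The absence of a stated confidence interval is not counted against it.

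**Conclusion.** The concern holds as a recommendation on efficiency and pre-specification. The planned comparison is valid but uses neither baseline FMA as a covariate nor the age factor, and two sections name different rules for the test. Under equal variances and r between 0.5 and 0.9, adjusting for baseline cuts the variance by 25% to 5% and would lift a true 80% power to between about 90% and 82%. If age is prognostic, including it also removes a conservative error in the standard error, of 0.5% to 11.8% for R² between 0.01 and 0.20. Type I error is not inflated in any of these cases. The direction is firm; the size in this trial is unknown, because r, R² and a coherent effect size and SD are all missing from the protocol.

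**What to change.** - Pre-specify one primary analysis: a linear model (ANCOVA) of 3-month FMA with group, baseline FMA and the age factor exactly as used in randomisation. Report the adjusted mean difference with a 95% confidence interval.
- Take the age cut-offs from the randomisation specification and state them. The age bands in the subgroup section {20b} are not said to be the randomisation strata and should not be assumed to be.
- Drop the normality-based choice of test. Keep the rank-sum test as a sensitivity analysis, and bring {20a} and {21b} into line.
- Use the same model form for NIHSS and BI.
- Time since stroke onset may be added as a covariate, but this is optional.

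The cost is analysis-plan wording, plus retrieving the cut-offs. Baseline FMA and age are already recorded, so no visit, procedure or participant is added. The change should be fixed before outcome data are seen by group.
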